### Sample size calculation

The power analysis concerns the primary research question. All computations are performed using GPower3.0 [49]. For the planned pair wise comparisons, to detect medium effects or larger (i.e., Cohen’s *d* ≥ 0.5; [50]) with at least 80% power and a Bonferroni corrected alpha of 0.025, a minimal sample size of 64 in each group is needed. With three groups (one experimental and two control groups) and 64 respondents per group, we also have at least 80% power to find effect sizes (*n*^*2*^) in excess of .05 (indicating a medium effect according to Cohen [50] using ANOVA.

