
### Aims

The main goal of this study is to evaluate the effectiveness of HT in reducing severe FOC, in comparison to (1) psycho education about pregnancy and childbirth, and (2) to care as usual. We also study how effectiveness is related to background variables including perceived distress, social support, and complications in pregnancy.

The following research questions are addressed:Do FOC women with severe FOC after HT treatment have a lower FOC than women who receive psycho education about pregnancy and childbirth via the internet or who have care as usual?Do women with severe FOC after HT treatment (1) have a better emotional bonding with their child during pregnancy and postpartum and (2) have fewer complications requiring forceps, vacuum extraction, or cesarean delivery and less third degree tears or episiotomy, (3) have lower levels of distress, depression, anxiety, PTSD symptoms and somatization, than women who receive psycho education about pregnancy and childbirth via the internet or who have care as usual?

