### Procedure

Recruitment takes place on the project’s internet website http://www.bevallingsbeleving.nl and by participating midwives, obstetricians and gynaecologists. During the routine check-up of pregnant women in gestation weeks 20–24, participating midwives and gynaecologists offer potential participants an information letter and/or a flyer that refers to the project’s internet website for registration for the study. Pregnant women show their informed consent by sending the completed approval form to the coordinating investigator, who returns the URL and login code to the participants by email. For the project a special safe internet environment has been developed, facilitating the completion of the online questionnaires. Inclusion of participants will take approximately three years, followed by one year to complete follow up measurements. The therapeutic intervention will be carried out by certified haptotherapists in various regions in the Netherlands. Admission in 20–24 weeks gestation will continue until at least 64 participants with a W-DEQ A score ≥ 85 have been included in each of the three arms respectively. At that time recruitment for the Comparison Group also stops.

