## Statistical analyses and power analysis

### Statistical analyses

To answer the primary research questions, we will use descriptive statistics (M and SD), between-subjects analysis of variance (ANOVA), followed by two planned pair wise comparisons (HT treatment versus care as usual, and HT treatment versus internetgroup).To maintain the experiment-wise Type I error rate at the 5% level, we use a Bonferroni corrected alpha of 0.05/2 = 0.025 for each single comparison. Clinical significance of the HT intervention will be tested both according to Jacobson and Truax’s criteria of reliable and clinical change [48] and by examination of the number of participants changing W-DEQ score from above to below a cut off score of 85. For the secondary research questions, we will use multiple regression, with `distress, depression, anxiety, somatization, PTSD symptoms, birth complications` as dependent variables, intervention (care as usual, psycho education via internet, and haptotherapy) as independent variable, and `background variables, social support, FOC` as covariates.

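### The claimed 80% power with 64 per group at alpha 0.025 holds only for one-sided comparisons, which the protocol never declares; two-sided it is 71%

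*Protocol article*

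**What the plan says.** The Statistical analyses section plans an ANOVA followed by "two planned pair wise comparisons (HT treatment versus care as usual, and HT treatment versus internetgroup"). For these it says "we use a Bonferroni corrected alpha of 0.05/2 = 0.025 for each single comparison", and gives the purpose as "To maintain the experiment-wise Type I error rate at the 5% level". The halving is therefore presented as a correction for two comparisons. Sidedness is not mentioned.

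The Sample size calculation section sets out "to detect medium effects or larger (i.e., Cohen’s *d* ≥ 0.5") and concludes that, "with at least 80% power and a Bonferroni corrected alpha of 0.025, a minimal sample size of 64 in each group is needed". Sidedness is not given there either. The next sentence, on the ANOVA, counts "64 respondents per group".

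The Procedure section keeps admission at 20–24 weeks of gestation open until a minimum of 64 women with severe fear "have been included in each of the three arms respectively". The Randomisation section allocates from a computer-generated list of the numbers 1, 2 and 3 and describes no blocking. The outcome is measured later, at week 36 of gestation and after delivery.

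The Aims section words the primary question in one direction: whether women after haptotherapy "have a lower FOC than women who receive psycho education about pregnancy and childbirth via the internet or who have care as usual".

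**The concern.** For a difference of 0.5 SD and 80% power, 64 per group is the familiar answer for a two-sided test at 0.05. A Bonferroni correction to 0.025 should raise the requirement, yet the stated number is the uncorrected one. If the tests are two-sided, the correction is claimed but is not in the sample size, and the two primary comparisons lack the power that the article gives them.

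The recruitment rule adds to this. It counts women entering the study, whereas power depends on women who supply the outcome.

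At stake is how a null result is understood. A reader who accepts 80% power for a medium effect will give a non-significant comparison more weight against such an effect than the design supports.

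**Working it through.** **Inputs.** Effect d = 0.5, power at least 80%, n = 64 per group (Sample size calculation). Alpha 0.025 per comparison, from 0.05/2 (Statistical analyses). Sidedness: not stated. Dropout: not stated, so any rate below is an assumption.

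**Formula.** For two equal groups, the noncentrality is d × √(n/2) = 0.5 × √32 = 2.83, with 2n − 2 = 126 degrees of freedom. Power is the probability that a noncentral t variable with these parameters passes the critical value.

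**Reproducing the stated figure, then the alternative**

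| Test | Critical t (126 df) | Power at 64 per group | Smallest n per group for 80% |
|---|---|---|---|
| One-sided 0.025 | 1.98 | 80.1% | 64 |
| Two-sided 0.05 (uncorrected) | 1.98 | 80.1% | 64 |
| Two-sided 0.025 | 2.27 | 71.2% | 78 |

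The first two rows share a critical value, so 64 alone cannot show which was used. Both reproduce the article; two-sided 0.025 does not. With 63 per group the first two rows fall to 79.5%. In the third row, 77 per group gives 79.8% and 78 gives 80.4%. Using the error term pooled over three groups (189 df) changes 71.2% only to 71.5%. With 64 per group at two-sided 0.025, the difference detectable with 80% power is 0.55 SD.

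**The ANOVA statement** was checked separately. With eta-squared 0.05 and N = 3 × 64 = 192, the noncentrality is 192 × 0.05/0.95 = 10.1, and power at alpha 0.05 is 81.3%. That claim reproduces.

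**Effect of the stopping rule.** Admission runs until the slowest-filling arm reaches 64. Simulating the rule with unrestricted 1:1:1 allocation (20,000 runs) gives mean ordered arm sizes of about 64, 71 and 78, or about 213 women in total. Average power for a haptotherapy comparison, with the loss applied equally to all arms:

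| Assumed loss | Two-sided 0.025 | One-sided 0.025 |
|---|---|---|
| none | 76% | 84% |
| 5% | 73% | 82% |
| 10% | 71% | 80% (79.7%) |
| 15% | 68% | 77% |
| 20% | 65% | 75% |

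If both compared arms had exactly 64 at entry, an assumed loss of 10%, 15% or 20% would leave 58, 54 or 51 analysed. Power would then be 66%, 63% or 60% two-sided, and 76%, 73% or 71% one-sided.

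**The case against.** The strongest reply is that the stated number is not an error at all. One-sided 0.025 reproduces 64 exactly, the primary question is directional, and two one-sided tests at 0.025 keep the total error within 5%. Nor does a non-directional omnibus F test settle the sidedness of two separately planned contrasts. This stands so far as it goes: the documents do not support the stronger inference that the 80% figure is simply wrong. It does not dispose of the point. A directional question is not a declared one-sided test, a bare alpha is conventionally read as two-sided, and the article explains the halving solely as a correction for two comparisons.

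A reader might also infer that recruitment stops at 64 per arm, so that any dropout takes even the one-sided reading below 80%. The documents do not support that. The rule sets 64 as a minimum for every arm, so the other two arms will usually be larger. Any loss at all breaks the one-sided reading only when both compared arms hold exactly 64. On average, one-sided power stays above 80% at an assumed 5% loss and reaches about 80% at 10%.

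Finally, a condensed article may leave an attrition allowance to the full protocol, so its absence here is not held against the plan. What remains is that the article's own power section and its recruitment rule count different things.

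**Conclusion.** As written, the power claim is conditional on a choice that the article does not make. If the pairwise tests are one-sided at 0.025, 64 analysed per arm gives 80.1% and the claim is right. If they are two-sided, as a reader would normally assume, it gives 71.2%, about nine percentage points less, and the design has 80% power only for about 0.55 SD.

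The larger arms expected under the recruitment rule raise average two-sided power before loss to about 76%, which is still short. That figure assumes simple 1:1:1 allocation. The gain is also a by-product of the stopping rule, not the basis on which the article states its power.

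The two-sided and one-sided figures for 64 per group rest only on the article's own inputs. The figures after loss rest on assumed dropout rates and should be read as a range.

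**What to change.** In the Statistical analyses and Sample size calculation sections, state whether the two pairwise tests are one-sided or two-sided.

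- **If two-sided:** replace the 80% claim with 71% power for d = 0.5, or 80% power for d of about 0.55, at two-sided 0.025 with 64 analysed per arm.
- **If one-sided:** say so explicitly, and say that the 5% experiment-wise rate is then spent in one direction.
- **In either case:** base the figure on the number expected to respond at the outcome, and make clear that the 64 in the Procedure section is the minimum per arm at inclusion.

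The cost is a change of wording and, on the two-sided reading, a less favourable stated power. Correcting the statement does not require extra enrolment.

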## Abbreviations

ANOVA: Analysis of variance
DSM-IV: Diagnostic and statistical manual of mental disorders IV
FOC: Fear of childbirth (as measured by the W-DEQ)
PRAM: Pictorial representation of attachment measure
Severe FOC: W-DEQ score ≥ 85
State-Anxiety related to childbirth: Situational fear of childbirth
Trait-Anxiety related to childbirth: Disposition to react with fear of childbirth
TES: Traumatic event scale
W-DEQ: Wijma delivery expectance/experience questionnaire
W-DEQ A: W-DEQ, Version A measures prepartum fear of delivery
W-DEQ B: W-DEQ, Version B measures postpartum fear of delivery
4DSQ: Four dimensional symptom questionnaire.
